### Missing data

All communities experience in-migration and out-migration. We will add new arrivals to the study but will not follow those leaving the clusters. We do not have reason to expect differential out-migration between intervention and control clusters. Self-selection (decision not to participate or not to answer certain questions) in the surveys is a concern. Those who opt not to respond may be less involved with safe motherhood initiatives – thus affecting the measured effect. Therefore, we will characterise subjects with missing data as far as possible and analyse the effect of missing data using the multiple imputation method in the Amelia II programme [52].

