### Participants

Eighty indigenous communities in four municipalities with a total of around 8000 households. The study will include all indigenous women who give birth or become pregnant during the study period, and their adult family members.

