### Outcome measures

For objective (1), the central concern is the added benefit of supporting traditional midwives in a context of non-inferior maternal and neonatal mortality. The limited size of the populations involved hinders mortality estimates and increases reliance on intermediate outcomes: birth problems among survivors of pregnancy in the past year. We will measure maternal mortality and morbidity and neonatal mortality through direct questions in each household.

Secondary outcomes (objective (2)) include (a) reduction of social disruption, indicated by gender violence against pregnant women and (b) improvement in intermediate outcomes towards more engagement of women in their culture of origin. The CASCADA model describes these intermediate outcomes in a results chain based on the theory of planned behaviour, overcoming the well-documented limitations of the Knowledge, Attitude and Practices (KAP) model [39, 40]: *C*onscious knowledge, *A*ttitudes, positive deviation from *S*ubjective norms, intentions to *C*hange behaviour, *A*gency (individual and collective), *D*iscussion/socialisation of possible action and, finally, *A*ction or change of practice [41]. Two randomised trials in Pakistan and Mexico, a cross-sectional study in Southern Africa, and a qualitative analysis of narratives in three Southern African countries have used the CASCADA model [42–46].

In this case, the CASCADA model will reflect conscious knowledge of the traditional midwife, a positive attitude about using her services, a positive deviation from a negative subjective norm about traditional midwifery, intention to change in a future pregnancy, the agency to implement these choices, discussion of the choices with partners and, ultimately, interaction with the supported traditional midwife.

The economic outcome measures (objective (3)) are described below under ‘Economic analysis’.

The study will have two measurement points: a baseline survey administered by trained bilingual indigenous interviewers (February and March 2015) and a follow-up survey using the same procedure and questions about pregnancy experiences and outcomes to women pregnant during the past year (May 2017). The period of inquiry for the final survey is defined to avoid any overlap with the pre-intervention period. Given the extent of the region, logistical constraints mean it is not feasible to have continuous or mid-term data collection.

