### Random allocation of the intervention

The total of 80 enumeration areas in the four municipalities are home to the four main indigenous groups (Fig. 3). If we allocated the intervention at the level of enumeration areas, we would expect a substantial contamination effect within each municipality (mothers from control enumeration areas going to authentic traditional midwives in the intervention enumeration areas) with strong spill-over influence within the same indigenous group served by the intervention midwives; through schools; and through local government or non-governmental organisations (NGOs) taking up the emerging evidence to guide interventions in control enumeration areas. This contamination would reduce the measured difference between control and intervention enumeration areas. To avoid this, the study will centrally randomise the intervention to two of the four municipalities (40 enumeration areas, 20 in each municipality).

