#### Principal analysis

With 80 communities allocated evenly between the intervention and control arms, the principal analysis of primary outcomes will follow intention-to-treat principles using a cluster *t*-test (everyone included in each cluster, per allocation). We will report outcomes as absolute event rates among intervention and control groups, risk difference with two-sided 95% confidence intervals (95%CIs) and one-sided 97.5% confidence intervals for the non-inferiority analysis, and relative risk reduction (RRR) with 95%CI [48]. The intracluster correlation coefficient (ICC) will be calculated by dividing the between-cluster variance by the variance within and between clusters. 

*Sensitivity analysis* will focus on the different ethnic groups and their accompanying government health services. It will also examine the four intervention components separately because, although all components are available for all participating midwives, we expect a range of implementation in practice.

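### No stated rule ties a birth to where the woman lived when it happened, so births before a move into or out of the intervention arm can be credited to the wrong exposure

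*Protocol article*

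**What the plan says.** Four parts of the protocol article bear on this point.

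- **Missing data.** It acknowledges movement in both directions ("All communities experience in-migration and out-migration") and sets the rule: "We will add new arrivals to the study but will not follow those leaving the clusters". Its only reassurance about balance concerns leavers: "We do not have reason to expect differential out-migration between intervention and control clusters".
- **Participants.** Eligibility covers "all indigenous women who give birth or become pregnant during the study period", with no condition on length or place of residence.
- **Outcome measures.** The follow-up survey puts "questions about pregnancy experiences and outcomes to women pregnant during the past year (May 2017"). The stated limit on that window is a calendar one: "The period of inquiry for the final survey is defined to avoid any overlap with the pre-intervention period".
- **Principal analysis.** The intention-to-treat set is described as "everyone included in each cluster, per allocation".

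Allocation is by whole municipality: "the study will centrally randomise the intervention to two of the four municipalities". The section on random allocation explains that this is meant to avoid contamination, which would shrink the measured difference between arms.

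**The concern.** Read together, these rules let a birth enter the analysis under an allocation the woman was not living under at the time. Suppose a woman gives birth in August 2016 outside the intervention area, moves to an intervention municipality in April 2017 and is surveyed there in May. Her birth falls inside the permitted calendar window, she is a new arrival and so is added, and she is analysed with her new cluster. Her birth took place under usual care but is scored as an intervention birth. A move from an intervention to a control municipality produces the mirror-image error.

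The plan guards exposure in time but not by place. The dilution that municipality-level randomisation was chosen to prevent can therefore return through the inclusion rule. This matters more here than in a superiority trial, because the maternal-health comparison is one of non-inferiority. If support for midwives did raise complications, mixing usual-care births into the intervention arm would make that excess look smaller.

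**Working it through.** **Step 1: which births are affected.**

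| Situation | Exposure at birth | Scored as | Misclassified? |
|---|---|---|---|
| Birth before arrival in an intervention municipality, from a control municipality or from outside the study | Usual care | Intervention | Yes |
| Birth in an intervention municipality, then a move to a control municipality | Intervention | Control | Yes |
| Birth before arrival in a control municipality, from outside the intervention area | Usual care | Control | No |
| Move within a municipality | Unchanged | Same arm | No |
| Arrival before the birth | Exposed at birth, perhaps for part of the pregnancy | Arm of residence at birth | No, on residence at birth |

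**Step 2: effect on the difference.** Let pI and pC be the true complication risks in the two arms, m the share of analysed intervention births that took place under usual care, and m0 the share of analysed control births that took place under the intervention. Assume movers have the same risk as other women under the same care.

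- Observed intervention risk = (1 − m)·pI + m·pC
- Observed control risk = (1 − m0)·pC + m0·pI
- Observed difference = (1 − m − m0)·(pI − pC)

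With m0 near zero this is (1 − m) times the true difference.

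- True difference zero: observed zero, so no bias from this source.
- Benefit as in the pilot: 9/91 − 57/248 = 9.9% − 23.0% = −13.1 points. At m = 5% this becomes −13.1 × 0.95 = −12.4 points, against the intervention.
- True excess of 15 points: 15 × 0.95 = 14.25 at m = 5%, and 15 × 0.90 = 13.5 at m = 10%.

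**Step 3: the plan's own figure.** The Sample size calculation section states 80% power at a 5% significance level for a 15% margin on birth complications. This cannot be reproduced from the text. The control rate, its between-cluster variation and the scale of the margin are not stated there, and the power figure is not shown. The birth counts do agree: 4 × 1438 = 5752. Nothing below depends on the 80%.

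**Step 4: effect on type I error at the margin.** Inputs:

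- Control rate 57/248 = 23.0% (pilot; assumed to apply, and used for both arms in the standard error).
- Two clusters of 1438 births per arm (Sample size calculation).
- k-statistic 0.011. The article gives it for skilled attendance only; it is assumed here for birth complications, read first as a coefficient of variation and then as an intracluster correlation.
- One-sided 97.5% interval (Principal analysis), so nominal error is 2.5%.
- Margin M = 0.15 × 23.0% = 3.4 points if relative, or 15 points if absolute.
- m = 1%, 5% or 10%: pure assumption.

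With k as a coefficient of variation, SE² = ½ × [2 × 0.2298 × 0.7702/1438 + 2 × (0.011 × 0.2298)²], so SE = 0.0114. With 0.011 as an intracluster correlation, SE = 0.0455.

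Type I error = Φ(M·m/SE − 1.96), or the noncentral t equivalent with 2 degrees of freedom. Example: relative margin, m = 5%, SE = 0.0114 gives M·m/SE = 0.0345 × 0.05/0.0114 = 0.151, and Φ(0.151 − 1.96) = 3.5%.

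| Margin, reading of 0.011 | m = 1% (normal / t) | m = 5% (normal / t) | m = 10% (normal / t) |
|---|---|---|---|
| Relative, coefficient of variation | 2.7% / 2.6% | 3.5% / 3.1% | 4.9% / 3.9% |
| Relative, intracluster correlation | 2.5% / 2.5% | 2.7% / 2.7% | 3.0% / 2.8% |
| Absolute, coefficient of variation | 3.4% / 3.1% | 9.7% / 6.2% | 26% / 12.5% |
| Absolute, intracluster correlation | 2.7% / 2.6% | 3.6% / 3.2% | 5.2% / 4.1% |

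**Step 5: how much movement a given m needs.** If arrivals and births are spread evenly over the recall year (an assumption), about half of new arrivals' births precede the move. Then m = 5% requires about 5%/0.5 = 10% of surveyed mothers in the intervention arm to have arrived within the year from outside that arm, and m = 1% requires about 2%.

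**The case against.** Three stronger readings are tempting, and the document does not support them.

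- *That pre-arrival births will be counted.* The article says new arrivals are added. It does not say which of their births are attributed to the cluster. The questionnaire is not reproduced, and a residence rule may sit in the full protocol or analysis plan. This stands as a limit on the claim: such births can be counted under the rules as published, and no more than that is shown. The point is still more than an omitted detail, because the inclusion rule and the analysis set are both stated without qualification, and together they lead to the misattribution.
- *That every new arrival dilutes the comparison.* Women who enter control municipalities from outside the intervention area had usual care and are correctly classed. Moves within a municipality change nothing. Large clusters keep the affected group small.
- *That the rule favours a non-inferior result.* This holds only if the intervention is truly worse. With no effect the dilution is neutral, and with a benefit of the kind the pilot suggested it works against the intervention. Harm is, however, the case a non-inferiority test exists to guard against, so the conditional point remains.

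It can also be argued that surveying current residents and analysing them by cluster allocation suits a pragmatic cluster trial. That is fair as a design philosophy. But intention to treat keeps clusters in their allocated arm; it does not require counting an event that occurred before the woman lived there.

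**Conclusion.** The point holds in limited form, as a cheap improvement. The published rules leave a gap by place that the calendar restriction does not close. Births before arrival in intervention municipalities, and births of women who changed arm, can be credited to the wrong exposure. Any true difference then shrinks by about (1 − m).

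The size is unknown and probably small. For an assumed m of 1% to 5%, type I error at a relative 15% margin goes from 2.5% to about 2.6–3.5% with 0.011 read as a coefficient of variation, and to no more than 2.7% with it read as an intracluster correlation. If the margin is 15 absolute points the rise is larger, up to 9.7% at m = 5% under the least conservative clustering and test assumptions. These figures rest on the pilot control rate, the borrowed k-statistic, movers having ordinary risk, and an invented range for m. They show direction and order of size and are not a forecast. What analysts could not do afterwards is undo the misattribution without residence data.

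**What to change.** Add two items to the May 2017 survey: where the woman lived when the birth occurred, and when she arrived in her present community. The article's protocol date of 28 February 2017 precedes that survey. State in the protocol that each birth is attributed to the study municipality of residence at birth, so that a birth in another study municipality goes to that municipality's arm. Exclude births outside all study municipalities from the primary set. Report the analysis of all surveyed women, by municipality of current residence, as a sensitivity analysis, together with the number of births reassigned or excluded in each arm. In the Missing data section, address in-migration as well as out-migration.

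The cost is a short addition to the questionnaire, a sentence or two in the protocol, and a slightly smaller primary analysis set.

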### Sample size calculation

Borrowing from the field of bioequivalence, equivalency trials and their statistical testing procedures focus on non-inferiority margins [53]. We expect that supporting traditional midwives does not result in worse primary outcomes of maternal health than does the available usual care in the region, principally because so few indigenous women in the study area access available services. Under the non-inferiority hypothesis, the trial might show equivalent or superior effects of the intervention [54]. The pilot study suggested additional benefits that secondary outcomes accrue from a culturally safe intervention. In the absence of previous studies in similar settings, we established a practical margin for non-inferiority-based discussion of findings with local authorities and indigenous communities. The resulting computation of study power illustrates the possibilities of demonstrating non-inferiority in these small communities of fixed size.

Based on 2013 data, we expected 5752 births across the four municipalities [55]. This study size is too small to use maternal mortality as an outcome over the funded duration of the trial, using 150% as the minimum non-inferiority margin to be detected. For birth complications as primary outcome, this study size can detect differences within a practical margin for non-inferiority of 15%, with 80% power at a significance level of 5% (Fig. 4).

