**Fig. 4 Fig4:**
[figure not shown]
Power of the sample in relation to the margin of non-inferiority for maternal mortality and birth complications

For the secondary outcome of improved skilled birth attendance (birth assisted by traditional midwife or physician), the pilot study suggested a rate of 92% in control communities (k-statistic 0.011). Follow-up of 1438 births in each cluster (two clusters per arm) would detect a 6.2% increase in skilled attendance (92.1% to 97.8%) with 80% power at a significance level of 5% (allowing us to set the non-inferiority margin at 15%).

These calculations assume no interaction effects with cluster as unit of primary analysis in unmatched parallel groups and relied on the trial simulator devised by Taylor and Bosch [56].

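### The stated power rests on 5752 births, which one past-year survey of about 8000 households cannot supply

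*Protocol article*

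**What the plan says.** Under Sample size calculation, the protocol states: "Based on 2013 data, we expected 5752 births across the four municipalities". The period that this count covers is not given. The same study size then supports two statements: that maternal mortality is out of reach, and that birth complications can be assessed against a 15% non-inferiority margin with 80% power at a 5% significance level. After Fig. 4, the skilled-attendance calculation reads "Follow-up of 1438 births in each cluster (two clusters per arm") and says that this "would detect a 6.2% increase in skilled attendance (92.1% to 97.8%) with 80% power at a significance level of 5"%.

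The population and the data source are described elsewhere. Participants gives "Eighty indigenous communities in four municipalities with a total of around 8000 households". Outcome measures provides for two surveys. The final one puts "questions about pregnancy experiences and outcomes to women pregnant during the past year (May 2017"), over a period chosen not to overlap with the time before the intervention. The same section adds that "it is not feasible to have continuous or mid-term data collection".

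**The concern.** The number of births in the power calculation should be the number that the design can observe. The protocol takes a municipal count and gives no step that converts it into births in the surveyed households within the recall year. It states no household size, birth rate or response rate. If the observable number is much smaller, the confidence interval for the primary non-inferiority comparison will be wider than the stated 80% power implies, and an inconclusive result becomes more likely than a reader would expect. The wording about following up 1438 births per cluster also describes an activity that the two-survey design does not contain.

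**Working it through.** **1. Where the planning size comes from.** 4 × 1438 = 5752 exactly. The per-cluster figure is therefore the municipal total divided equally by four.

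**2. Against the surveyed population** (8000 households and 80 areas, from Participants).
- 5752 / 8000 = 0.72 births per household in the recall year.
- 5752 / 80 = 72 births per area of about 100 households.
- If births over two years were all captured: 0.72 / 2 = 0.36 per household-year.
- Assuming 4 to 7 persons per household, 0.72 per household means about 180 down to 103 births per 1000 people in a year. The two-year reading means about 90 down to 51 per 1000. The one-year rates are not credible, and the two-year rates still exceed the 25 to 40 per 1000 assumed below.

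**3. What one year could yield.** Births = households × persons per household × birth rate. Persons and rate are my assumptions.
- Low: 8000 × 4.5 × 0.025 = 900, or 225 per municipality.
- High: 8000 × 6 × 0.040 = 1920, or 480 per municipality.
- Excess: 5752 / 1920 = 3.0 and 5752 / 900 = 6.4. On a two-year reading: 5752 / 3840 = 1.5 and 5752 / 1800 = 3.2.
- A wider grid (4 to 7 persons, 20 to 40 per 1000) gives 640 to 2240 births, an excess of 2.6 to 9.0 times.

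I use 350 births per municipality (1400 in all) as a working value inside the 900 to 1920 range.

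**4. Skilled attendance.** Inputs: 92.1% against 97.8%, two clusters per arm, m births per cluster, and the stated clustering value of 0.011 read as an ICC. SE² = [p0(1−p0) + p1(1−p1)] × [1 + (m−1) × 0.011] / (2m). Power = Φ(0.057/SE − 1.645), that is, one-sided 5% with a normal approximation.
- m = 1438: design effect 16.8, SE 0.0235, power 78%. Of the readings tried, this comes closest to the stated 80%.
- m = 350: design effect 4.84, SE 0.0255, power 72%.
- Cutting births 3- to 6-fold gives 74% down to 69%.

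**5. Birth complications.** The base rate, margin scale and ICC are not in the text, and Fig. 4 is not shown, so the stated 80% has no unique reproduction. I use two base rates from the pilot: the controls, 57/248 = 23.0%, and both arms pooled, (9 + 57)/(91 + 248) = 66/339 = 19.5%. Equal true rates and one-sided 2.5% (from Principal analysis) are assumed. SE² = 2p(1−p) × [1 + (m−1) × ICC] / (2m). Power = Φ(margin/SE − 1.96).

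| Margin and clustering | Base rate | m = 1438 | m = 350 |
|---|---|---|---|
| 15% relative, none | 19.5% | 80% | 28% |
| 15% relative, none | 23.0% | 87% | 33% |
| 15 points absolute, ICC 0.011 | 19.5% | 94% | 90% |
| 15 points absolute, ICC 0.011 | 23.0% | 91% | 86% |

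The first row gives 80% at the full 5752 births. That is consistent with the count having been used in this way, but does not prove it.

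**6. Maternal deaths** at 281 per 100,000 (The setting): 5752 × 0.00281 = 16.2, against 1400 × 0.00281 = 3.9.

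**The case against.** Several objections carry weight.

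- **Births did not drive recruitment.** The protocol presents the power computation as an illustration for communities of fixed size, so a smaller count changes no design step. This stands, but a stated power should still match the births that the design can observe.
- **A longer window might apply.** Participants says "The study will include all indigenous women who give birth or become pregnant during the study period". A reader could infer that all births over two years count. The final survey asks only about the past year, no collection takes place between the surveys, and the baseline survey covers only births before the intervention. Even two full years would leave 0.36 births per household-year.
- **The areas might be the whole municipalities.** "The total of 80 enumeration areas in the four municipalities are home to the four main indigenous groups" could be read that way. That does not help, because the household total is still about 8000.
- **A general collapse of power is not shown.** A reader might infer one from the fall to 28% or 33%. Those figures need a relative margin and no clustering. The protocol does not state the margin scale, and it reports non-inferiority as a risk difference. With an absolute margin and an ICC of 0.011, power stays above 80% at 350 births per municipality. For skilled attendance, variation between municipalities dominates, so births per cluster matter little.
- **The mortality statement is not overturned.** The protocol says that the trial is too small for maternal mortality, and fewer births strengthen that.
- **Scaling up the pilot is weak support.** It had 94 + 252 = 346 women in one of these municipalities, and 4 × 346 = 1384 falls in the range above. But nothing shows that the pilot covered that municipality's 20 trial areas, or that the other three municipalities resemble it.

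**Conclusion.** The mismatch holds on the protocol's own figures: 5752 births do not fit about 8000 households and a one-year recall survey. The excess of about 3 to 6.4 times (1.5 to 3.2 on a two-year reading) rests on assumed household size and birth rate and is not a figure from the protocol. The effect on power ranges from a few percentage points, with an absolute margin and an ICC of 0.011, to a loss of more than 50 points, with a relative margin and no clustering. The text does not settle which applies. For skilled attendance the loss is about 6 points under the closest reading. How far two clusters per arm limit power is a separate question, and none of the loss shown here is attributed to it.

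**What to change.** In Sample size calculation, replace 5752 and 1438 with the births expected in the 80 surveyed areas within the one-year recall window. Give them by municipality and do not assume that they are equal. The baseline survey, scheduled for February and March 2015, should supply the counts, since the protocol version is dated February 2017. Recompute the stated power for birth complications and skilled attendance. State the margin scale (absolute or relative), the ICC and the sidedness used. Restate the mortality sentence on the smaller count; its conclusion stays. Remove the wording that 1438 births per cluster are followed up. No design or data-collection change is needed: the cost is recalculation and less favourable stated figures.

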The pilot showed that a larger trial would be feasible. It allowed us to adjust the intervention, to design and test questionnaires, to establish the local capacity needed to conduct a larger study, and to identify costs of the intervention. The pilot established the acceptability of the intervention according to three criteria. First, the intervention was safe; the groups with midwives receiving support did not have worse health outcomes and did not report complicated cases related to the intervention (see below). Second, the communities did not react against the recovery of traditions; some previous experience had suggested that some community members, particularly the younger ones, might interpret an intervention to support traditional midwives as an attempt to reduce the services provided by the Government. Third, the staff at the local healthcare centres accepted an increased involvement of midwives with no conflicts which would make the health authorities stop the intervention.

The pilot found similar levels of *pregnancy* complications between women in exposed communities (24/94) and controls (65/252) (OR 0.99, 95%CI 0.52–1.71). It was not intended to measure mortality but, in the event, results were compatible with a positive effect of supporting traditional midwives on reducing *birth* complications (9/91 exposed and 57/248 controls reported birth complications, OR 0.37, 95%CI 0.11–0.73). Women living in the intervention area did not report any neonatal deaths during the last year of the intervention (0/93, compared with 6/254 in control area, chi-square = 2.2, *p* = 0.13). The pilot also suggested advantages for women in terms of skilled birth attendance (92/94 among exposed and 233/253 among controls were assisted by a traditional midwife or physician, OR 3.95, 95%CI 1.0–15.59).

The significantly lower birth complications in intervention communities were likely due to two factors: (1) improved referrals as a result of the intercultural brokerage; and (2) increased use of traditional midwives in the intervention area, resulting in fewer women giving birth without a skilled birth attendant. The pilot demonstrated acceptability of the intervention among the communities and the economical and logistical feasibility of supporting traditional midwifery. The pilot also built local capacity for intercultural and multi-disciplinary research that is scientifically valid and also takes full account of the local cultural context.

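### If the 15% margin is relative, a cluster t-test on the four randomised municipalities cannot reach the stated 80% power for birth complications

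*Protocol article*

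**What the plan says.** Under Sample size calculation, the protocol article gives the number of births: "Based on 2013 data, we expected 5752 births across the four municipalities". It then claims for birth complications that "this study size can detect differences within a practical margin for non-inferiority of 15%, with 80% power at a significance level of 5" per cent. This sentence gives no event rate, no margin scale, no sidedness and no between-cluster variance for the outcome.

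The same section, after Figure 4, turns to skilled attendance and describes the structure as "Follow-up of 1438 births in each cluster (two clusters per arm"). That is 4 × 1438 = 5752 births. The only clustering figure printed, k = 0.011, belongs to skilled attendance. The section closes by saying "These calculations assume no interaction effects with cluster as unit of primary analysis in unmatched parallel groups".

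Random allocation of the intervention fixes the randomised unit: "the study will centrally randomise the intervention to two of the four municipalities (40 enumeration areas, 20 in each municipality").

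Principal analysis counts clusters differently: "With 80 communities allocated evenly between the intervention and control arms, the principal analysis of primary outcomes will follow intention-to-treat principles using a cluster" *t*-test. It also plans a one-sided 97.5% confidence interval for non-inferiority.

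The only birth-complication rates in the article come from the pilot: "9/91 exposed and 57/248 controls reported birth complications".

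**The concern.** This is the only power claim for the primary outcome on which non-inferiority is to be judged, since the article itself sets mortality aside as too rare. The claim is tied to a design with two clusters per arm. A t-test on four cluster summaries has 2 degrees of freedom, so its critical value is 4.30 where a large-sample test uses 1.96. That penalty applies however many births each municipality contributes. If the margin is relative, it amounts to only about three percentage points on rates near 20%.

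If the printed 80% does not belong to the test that will be run, an inconclusive confidence limit would be read as the result of a well-powered trial. In fact the trial might have had little chance of showing non-inferiority even with identical arms.

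**Working it through.** **Inputs.** There are 5752 births, so 2876 per arm. The pilot control rate is 57/248 = 0.2298. The pooled pilot rate is (9 + 57)/(91 + 248) = 66/339 = 0.1947. The article does not say which rate it used, so both are shown. The one-sided level is 2.5% (Principal analysis), with 5% shown as an alternative because the power sentence gives no sidedness. The arms are taken as truly equal and the clusters as equal in size.

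**Margin scale.** Two neighbouring figures favour a relative margin. A 150% margin for mortality can only be relative. The skilled-attendance rise described as 6.2% runs from 92.1% to 97.8%, which is 5.7 points, and 5.7/92.1 = 6.2%. The relative margin is then 0.15 × 0.2298 = 0.0345 (control rate) or 0.15 × 0.1947 = 0.0292 (pooled rate).

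**Attempt to reproduce 80%, births treated as independent.** SE = √[2p(1−p)/2876], and power = Φ(margin/SE − 1.96).
- Pooled rate: SE = 0.01044, ratio 2.797, power Φ(0.837) = 79.9%.
- Control rate: SE = 0.01109, ratio 3.107, power Φ(1.147) = 87.4%.

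One of the two rates matches the printed figure. The objection takes up what that does and does not show.

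**Cluster t-test, general form.** With K clusters per arm and m births per cluster, SE² = 2[p(1−p)/m + σ²_b]/K and df = 2K − 2. Power is the upper tail of a noncentral t with noncentrality margin/SE. The between-cluster variance σ²_b is (k·p)² or ICC·p(1−p).

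**Four municipalities (K = 2, m = 1438, df = 2), relative margin.** With σ²_b = 0 the noncentralities are again 2.797 and 3.107, but the critical value is 4.303 (one-sided 2.5%) or 2.920 (one-sided 5%).

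| Between-cluster variation | Pooled rate, 2.5% | Control rate, 2.5% | Pooled rate, 5% | Control rate, 5% |
|---|---|---|---|---|
| none | 35% | 41% | 57% | 64% |
| k = 0.011 (borrowed from skilled attendance) | 34% | 39% | 56% | 62% |
| ICC 0.001 (illustrative) | 19% | 22% | 34% | 38% |

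Any positive variance lowers power, so the first row is the ceiling and 80% is out of reach. At one-sided 2.5% and 2 df, 80% power needs a noncentrality of about 5.65. With zero variance the relative margin would therefore have to be at least 5.65 × 0.01109/0.2298 = 27% (control rate) or 5.65 × 0.01044/0.1947 = 30% (pooled rate).

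**Eighty communities (K = 40, m = 71.9, df = 78), relative margin, one-sided 2.5%.**

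| ICC (illustrative) | Pooled rate | Control rate |
|---|---|---|
| 0 | 79% | 87% |
| 0.005 | 66% | 75% |
| 0.01 | 56% | 65% |
| 0.02 | 42% | 50% |

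At k = 0.011 the figures stay at 79% and 87%.

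**Absolute margin of 15 points, four municipalities, one-sided 2.5%.** Power is close to 100% with no between-cluster variance or at k = 0.011. It comes down to 80% at k of about 0.105 (control rate) or 0.125 (pooled rate), some ten times the only k printed.

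**The case against.** The strongest reply is that the article says the cluster was the unit and that a trial simulator was used. The power curve is in a figure that is not available here, so a between-cluster variance for birth complications may well have been used. That stands, and it bears directly on the 79.9% match. A reader might infer from the match that the sample size was computed for independent births and clustering was ignored. The documents do not support that inference. The match needs the pooled pilot rate, which the article never states, while the more usual control rate gives 87%. Clustered settings also return about 80%: 40 against 40 communities at the control rate with an ICC of about 0.003 (k about 0.097) on the relative margin, or 2 against 2 municipalities with k about 0.105 on an absolute margin. The origin of the 80% cannot be determined from the text.

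A second reply is that Principal analysis introduces the t-test with 80 communities, and at the only printed k that test has 79% to 87% power. This also stands as arithmetic, so it would be wrong to say that the planned test must have far less power whatever the unit. With communities as the unit, the loss depends on ICCs that are assumptions here. But municipalities, not communities, were randomised. A t-test on communities treats those within one municipality as independently allocated, and the sample size text itself counts two clusters per arm.

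A third reply is that the margin may be absolute, since a risk difference will be reported. The text does not exclude this. On that reading, 80% is reached on four municipalities for any k up to about 0.105 to 0.125, and the conflict disappears. The neighbouring figures point the other way, and such a margin would accept a rise from 23% to 38%.

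A condensed article may leave planning inputs to a fuller document. The point here is different: a printed power figure and the printed design do not fit together on the reading that the text favours.

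**Conclusion.** The point holds in a conditional form. If the 15% margin is relative, the stated 80% power cannot be achieved by a cluster t-test on the four randomised municipalities at any between-cluster variance. The ceiling is 35% to 41% at the planned one-sided 97.5% limit and 57% to 64% at one-sided 5%. This rests on the pilot rates, equal arms, equal cluster sizes and all 5752 births being observed. It needs no assumed ICC and no view on how the 80% was derived.

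Two things limit it. With the 80 communities as the unit, the printed figure is attainable at very small ICCs and falls to 56% to 65% at 0.01, but that analysis does not use the randomised unit. With an absolute margin the figure is attainable on four municipalities. Because the article fixes neither the margin scale nor a single unit of analysis, a reader cannot rely on the 80% as it stands.

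**What to change.** 1. Reconcile the unit of analysis between Random allocation, Principal analysis and Sample size calculation: four municipalities or 80 communities. If communities are kept, say how the analysis accounts for randomisation by municipality.
2. State whether the 15% margin is relative or absolute.
3. Recompute power for the cluster *t*-test on that unit at the one-sided 97.5% limit. Use the control rate and the between-cluster variance of birth complications from the February–March 2015 baseline survey. Four municipalities estimate that variance poorly, so show a range.
4. Replace the 80% with the result, or give the margin at which 80% is reached. If Figure 4 used a between-cluster variance for this outcome, print it beside the margin.

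The cost is a re-run on baseline data scheduled for collection in 2015 and a short restatement, with no extra participants. The downside is that the stated power will probably be less favourable.
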